#### Descriptive Information

We will capture date of birth, sex, marital status, height and weight. Body mass index will be calculated as weight (kg)/height × meters^2^. The Functional Comorbidity Index will be used to estimate comorbidities associated with physical functioning [60]. We will determine pre-fracture function during the week prior to fracture; and will screen for depression [61], and monitor pain and fatigue [62].

### Quality of Life and Health Resource Utilization Measures

We will use the EQ-5D-5L, a generic health related quality of life measure [63]. This five question measure is easy to administer and can be used in cost-effectiveness studies to evaluate clinical interventions [63]. Respondents are asked to rate their health states for mobility, self-care, usual activities, pain/discomfort and anxiety/depression. We will use a capability measure, the ICECAP-O [64] to determine the effect of the intervention on participants' quality of life. We will also use a modified health resource utilization questionnaire [65] to capture self-report direct and indirect costs.

### Process Evaluation

We will use a log to record all eligible participants and will document reasons for ineligibility or refusal to participate. Adherence to the B4 Clinic will be monitored over the course of the intervention, and adverse events monitoring will occur throughout the study. We will invite participants to complete an exit interview to examine satisfaction with components of the intervention. We will also explore barriers and enablers to participation in the Clinic services; and specifically we will examine reasons for low attendance. Finally we will complete open-ended qualitative interviews with clinical and research staff throughout the study to document our progress. Members of the research team will review the findings from these interviews and adjust research administrative procedures if necessary and appropriate.

### Statistical Analysis

#### Sample Size

We plan to recruit 130 participants over an 18-month period. Allowing for 15% loss to follow-up we will have 110 evaluable participants at 12 months. We have chosen to power the study to detect fairly large effect sizes as the proposed intervention represents an intensive use of scarce resources (geriatrician, physical therapists) and would need to demonstrate large effects to be considered for adoption by health funders. *Justification for sample size*: Given the anticipated presence of ceiling and/or floor effects in the SPPB we will compare the two groups, without adjusting using a Wilcoxon-Mann-Whitney (WMW) test. The WMW test can be characterized by the WMW odds ratio, OR_wmw _= π/(1-π) where π = Pr (Y_1 _< Y_2_) + 0.5 Pr (Y_1 _= Y_2_). Note, if there is no difference between the groups, π = 0.5 or equivalently, OR_wmw _= 1.0. If the OR_wmw _is 2.0, the odds are 2:1 that Y_1 _is less than Y_2, _i.e. π = 2/3. With 55 evaluable participants/group we will have >80% power to detect ORs of 2.0 or greater assuming α = 0.05 (2-sided) [66].

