### Outcomes

#### Data Collection Protocol

Measurements will be conducted at the Centre for Hip Health and Mobility, Vancouver Coastal Heath Research Institute on the Vancouver General Hospital site or at a participant's home at baseline (3 months post-surgical repair), 6 and 12 months.

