#### Primary analysis

All analyses will be intention-to-treat; there will be no interim analysis. SPPB at 12 months post randomization will be compared between the two groups using the Wilcoxon-Mann-Whitney test. Point and interval estimates for the difference in medians will be calculated.

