#### Secondary analyses

All secondary analyses will be for descriptive purposes only. Point and interval estimates of the effect of the intervention on LEM scores at 6 and 12 months will be determined using a linear mixed model. The baseline LEM score will be included in the model as a covariate. Analyses for frailty, TUG and activity patterns as measured by CHAMPS and accelerometry will follow that of LEM. Types of management received and adherence to prescribed therapies will be described separately for each group. Analyses will be conducted at 6 months for descriptive purposes only.

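### The primary SPPB test is fixed as unadjusted although a pre-randomisation SPPB appears to be available; the test is valid and adequately powered, but gives up efficiency

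*Protocol article*

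**What the plan says.** The Sample Size section of the protocol article sets the primary comparison and gives a reason for the method. It begins "Given the anticipated presence of ceiling and/or floor effects in the SPPB" and continues "we will compare the two groups, without adjusting using a Wilcoxon-Mann-Whitney (WMW) test". The Primary analysis section repeats the choice: "SPPB at 12 months post randomization will be compared between the two groups using the Wilcoxon-Mann-Whitney test". It names no covariate and promises point and interval estimates for the difference in medians.

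The Data Collection Protocol section schedules measurements "at baseline (3 months post-surgical repair), 6 and 12 months". The Randomization section has the coordinator obtain the allocation once the baseline assessment is finished, with stratification by hospital site and sex. Neither section lists SPPB by name as a baseline measurement.

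The Secondary analyses section treats baseline differently: "The baseline LEM score will be included in the model as a covariate". Frailty, TUG and activity follow the LEM approach. All of these analyses are labelled descriptive.

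**The concern.** The one confirmatory comparison in the trial ignores the baseline value of its own outcome, while several descriptive analyses use theirs. It also ignores the two stratification factors.

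The reason given does not lead to that choice. Bounded and heavily tied scores argue against a normal-theory comparison of means. They do not argue against a covariate, because a rank analysis of covariance or a proportional-odds model can handle bounds, ties and a baseline score together.

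At stake are the power of the primary test, most of all for effects smaller than the one planned for, and the precision of the estimate.

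This is not a detail left to an unseen analysis plan. The article states positively that there will be no adjustment.

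**Working it through.** **Inputs from the protocol article (Sample Size).** OR_wmw = 2.0, so π = 2/3; two-sided α = 0.05; 130 recruited with 15% loss; "With 55 evaluable participants/group", so N = 110.

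**Input not in the document.** The correlation r between baseline and 12-month SPPB. It is assumed and shown from 0.2 to 0.7.

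**Step 1: reproduce the plan's figures.** 130 × 0.85 = 110.5, which agrees with 110 evaluable. Noether's formula for 1:1 allocation is

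power = Φ(√(3N) × (π − 0.5) − 1.96).

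With N = 110: √330 = 18.17; 18.17 × 0.1667 = 3.03; 3.03 − 1.96 = 1.07; Φ(1.07) = 85.7%. The claim of more than 80% holds. The total needed for 80% power is (1.96 + 0.842)² / (3 × 0.1667²) = 94.2, so 110 leaves a small reserve. A cross-check through a normal shift of √2 × z(2/3) = 0.609 SD, with the Wilcoxon efficiency of 3/π (here the constant 3.14…), gives 87.7%.

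**Step 2: adjust for baseline.** Adjustment multiplies the variance by about 1 − r². Power becomes Φ(√(3N/(1 − r²)) × (π − 0.5) − 1.96), and interval width is multiplied by √(1 − r²). For r = 0.5: √(330/0.75) = 20.98; 20.98 × 0.1667 − 1.96 = 1.54; Φ(1.54) = 93.8%.

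| Assumed r | Power at OR_wmw 2.0 | Relative interval width | Evaluable N for 80% power |
|---|---|---|---|
| unadjusted | 85.7% | 1.00 | 94 |
| 0.2 | 87.1% | 0.98 | 90 |
| 0.3 | 88.8% | 0.95 | 86 |
| 0.5 | 93.8% | 0.87 | 71 |
| 0.7 | 98.9% | 0.71 | 48 |

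**Step 3: a smaller effect.** At OR_wmw 1.6, π = 1.6/2.6 = 0.615. Unadjusted: 18.17 × 0.115 − 1.96 = 0.14, so power is about 55%. The same formula gives about 59% (r = 0.3), 68% (r = 0.5) and 83–84% (r = 0.7).

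**Step 4: do ceiling effects remove the gain?** A simulation used a whole-number score from 0 to 12 with latent SD 2.7 and 55 per group, with the shift calibrated to π = 2/3. It compared the unadjusted test with a rank analysis of covariance on baseline ranks, with 4,000 trials per power setting and 2,000 per null setting.

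| Controls at ceiling | r | Unadjusted | Rank ANCOVA |
|---|---|---|---|
| 5% | 0.3 | 88% | 90% |
| 5% | 0.5 | 86% | 93% |
| 5% | 0.7 | 89% | 99% |
| 23% | 0.3 | 89% | 91% |
| 23% | 0.5 | 89% | 94% |
| 23% | 0.7 | 89% | 99% |

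The gain survives a marked ceiling. Type I error lay between 3.9% and 5.8% for the two methods, where simulation error alone has a standard error of √(0.05 × 0.95/2000) = 0.5 points. No proportional-odds model was simulated.

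**The case against.** The strongest reply is that nothing here is wrong. An unadjusted rank test in a randomised trial is valid, it is pre-specified, the two sections agree on it, and it meets its power target. The larger gains arise below OR_wmw 2.0, and the article deliberately plans for large effects because funders would require them. A simple primary test beside modelled, descriptive secondary outcomes is a coherent choice. All of this stands. It limits the point to efficiency but does not supply a reason for omitting baseline.

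The size of the gain is also open. The article gives no correlation, and baseline is taken early in recovery, so r could be low. At r = 0.2 adjustment adds little more than one power point. This stands too, and is why the range starts there.

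Adjustment has a price. A rank analysis of covariance gives a test but no direct effect in SPPB points. A proportional-odds model gives an odds ratio conditional on baseline, under a proportionality assumption. That is not the marginal OR_wmw on which the sample size rests, nor the difference in medians promised in the Primary analysis section. This stands and must be dealt with in the wording.

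A reader might infer that chance baseline imbalance would bias the unadjusted result. It would not: the test and interval already allow for such imbalance, so this is the precision point in another form.

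**Conclusion.** The point holds as a recommendation about efficiency. At the planned effect, adjustment for baseline would add about 1 to 13 power points for assumed correlations of 0.2 to 0.7, and narrow an adjusted interval by about 2 to 29%. It rests on two things the article does not state outright: the correlation, and that SPPB is among the baseline measurements. The second is a sound inference from the measurement schedule and the order of baseline assessment and allocation.

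Three stronger readings are tempting and unsupported:

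- That the trial is underpowered or its primary test invalid. Power is about 86% against a claim of more than 80%, and the test is valid.
- That the loss is certainly substantial. At r = 0.3 it is about 3 points.
- That baseline was dropped for no reason. A reason is given, but it supports a rank method and not the omission of the covariate.

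**What to change.** Before unblinding:

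- Make the primary test a rank analysis of covariance of 12-month SPPB on baseline SPPB, ideally also including the stratification factors, site and sex.
- Keep the unadjusted Wilcoxon-Mann-Whitney test as a sensitivity analysis.
- Still report the marginal OR_wmw and the difference in medians, each with an interval, and state which effect measure accompanies the primary test. If those estimates are left unadjusted, their intervals will not narrow; the precision gain applies only to a baseline-adjusted estimate. If a proportional-odds model is preferred, say that its odds ratio is conditional on baseline and rests on proportionality.
- Name SPPB explicitly among the baseline measurements.

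The sample-size statement can stay, as a conservative figure. The cost is redrafting of the analysis text, including the effect measure and its link to the sample-size target. If baseline SPPB is collected as implied, no new data or participants are needed.

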#### Primary analysis

All analyses will be intention-to-treat; there will be no interim analysis. SPPB at 12 months post randomization will be compared between the two groups using the Wilcoxon-Mann-Whitney test. Point and interval estimates for the difference in medians will be calculated.

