#### Primary Outcome

Our primary outcome for this trial is mobility as measured by the Short Physical Performance Battery (SPPB) at 12 months. This valid and reliable measure of mobility has been developed with older adults to assess balance and other key lower extremity functions [44]. The SPPB is composed of three separate tests that are timed and categorized depending on performance: the tests include standing balance, gait speed and sit to stand performance. The SPPB can predict future disability in older adults [45].

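### The only effect estimate named for the primary outcome is a difference in medians, but the primary test and the sample size rest on the WMW probability π and its odds ratio, and the two need not agree

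*Protocol article*

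**What the plan says.** Under Primary analysis the test is fixed: "SPPB at 12 months post randomization will be compared between the two groups using the Wilcoxon-Mann-Whitney test". The next sentence names the accompanying effect estimate: "Point and interval estimates for the difference in medians will be calculated". No other effect measure is named for the primary outcome.

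The Sample Size section works on a different scale. It explains the choice of test by the expected shape of the data ("Given the anticipated presence of ceiling and/or floor effects in the SPPB we will compare the two groups") and then says "The WMW test can be characterized by the WMW odds ratio". It defines OR_wmw as π/(1-π), where π is the probability that an observation from one group lies below one from the other, with ties counted as one half. Power is stated as above 80% for OR_wmw of 2.0 or more (π = 2/3), with 55 evaluable participants per group and two-sided α of 0.05.

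Under Primary Outcome the score is described as follows: "The SPPB is composed of three separate tests that are timed and categorized depending on performance". It is therefore built from categories, and ties are to be expected.

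**The concern.** The WMW test assesses whether π differs from 0.5. It is a test of the difference in medians only if the two distributions have the same shape and differ by a shift. The article states no such assumption, and the ceiling or floor effects that it gives as its reason for the test would break it: scores pile up at a limit and cannot move further.

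The p-value and the reported estimate would then answer different questions. A significant primary test could be published beside an interval that touches or covers zero, and readers would have to decide which to believe. The result would also not be on the scale used for planning. The article explains its choice of a fairly large effect by saying that the intervention "would need to demonstrate large effects to be considered for adoption by health funders". Readers will want to set the observed effect beside the planning value, and a median difference in points cannot be compared with an OR_wmw of 2.0.

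**Working it through.** **Inputs from the article:** 130 recruited, 15% loss, 110 evaluable (55 per group), two-sided α = 0.05, OR_wmw = 2.0, so π = 2/3.

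**Assumptions, not in the article:** SPPB is an integer score from 0 to 12, generated by rounding and capping a normal variable. In the runs tabulated below its control mean is 7 to 10 and its SD 2.5 or 3. The article gives neither a range nor a distribution, and it names no interval method.

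**Step 1. The plan's own figures.**
- Evaluable: 130 × 0.85 = 110.5, which agrees with 110.
- Power (Noether): Φ(√(12 × 0.25 × 110) × |2/3 - 1/2| - 1.96) = Φ(18.17 × 0.1667 - 1.96) = Φ(1.07) = 85.7%. The claim of more than 80% is reproduced.

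**Step 2. Equal medians with a real WMW effect.** A hypothetical ceiling case: the control group has 12% at each of 4, 6, 8 and 10 and 52% at 12; the intervention group has 14% at 10 and 86% at 12. Both medians are 12. But
- π = 0.86 × (0.48 + 0.5 × 0.52) + 0.14 × (0.36 + 0.5 × 0.12) = 0.6364 + 0.0588 = 0.695
- OR_wmw = 0.695/0.305, about 2.3.

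The true difference in medians is 0, while WMW with 55 per arm rejects in over 99% of simulated trials.

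**Step 3. How often test and interval conflict at the design effect.** 55 per arm, true OR_wmw = 2.0, percentile-bootstrap 95% interval for the median difference. The last column uses a 95% interval for OR_wmw instead (placement-value variance, logit scale), from a separate set of runs in the same settings.

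| Control mean, SD (before rounding) | WMW p<0.05 | Median interval excludes 0 | p<0.05 but interval includes 0 | As share of significant trials | OR_wmw interval disagrees with test |
|---|---|---|---|---|---|
| 7, 2.5 | 88.3% | 35.8% | 52.5% | 52.5/88.3 = 59% | 0.4% |
| 8, 3 | 88.8% | 41.5% | 47.3% | 47.3/88.8 = 53% | 0.4% |
| 9, 3 | 88.9% | 43.5% | 45.4% | 45.4/88.9 = 51% | 0.6% |
| 10, 3 | 89.7% | 48.8% | 40.9% | 40.9/89.7 = 46% | 0.4% |

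Repeat simulations over similar settings widen the share of significant trials to roughly 44-64%. An interval built from an order-statistic standard error gave about 26%.

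**Step 4. What the conflicts look like.** In the bootstrap runs nearly all of them have a lower limit of exactly 0. The lower limit was below 0 in only 1-6% of significant trials. A non-significant WMW test with a median interval excluding 0 did not occur.

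**Step 5. What OR_wmw would show.** At true OR_wmw = 2.0 the typical 95% interval runs from about 1.3 to 3.2. The smallest significant estimate, without tie correction, is π = 0.5 + 1.96 × √(111/(12 × 55 × 55)) = 0.608, so OR_wmw = 0.608/0.392, about 1.55. A p-value below 0.05 therefore does not place the result relative to 2.0, but the estimate and its interval do.

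**The case against.** The confirmatory decision is the WMW test, and nothing about it is wrong: test, α, sample size and power are sound. A summary in SPPB points is a reasonable thing to give clinicians and funders. Most of the conflict found above consists of intervals such as 0 to 3, which include zero only at the boundary. This comes largely from an integer score combined with a percentile bootstrap. Another method roughly halves the rate, and an article may leave the method to the analysis plan. All of this stands, and it limits both the size and the severity of the point.

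It can also be said that the article does not call the median difference the only estimate, and that π is U/(n₁n₂), so it follows from the test statistic. That is fair. It cannot be said that OR_wmw will never be reported. But the article does commit to one named estimate, and that estimate is on a different scale from the test, so this is a stated choice and not a detail left for later.

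Reading the phrase loosely as a Hodges-Lehmann shift does not remove the problem. On this tied, capped scale that interval conflicted with the test in 33-72% of simulated trials at OR_wmw = 2.0.

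Three stronger readings are tempting and are not supported:
- **That 2.0 is an adoption threshold.** The article uses 2.0 for power and explains in general terms why a large effect was chosen. It sets no success criterion at 2.0. That significance is reached below the planning value is normal in any powered trial.
- **That the two can conflict in either direction.** Only significant tests with intervals including 0 were seen.
- **That the primary test or its power is undermined.** Neither is.

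**Conclusion.** The point holds as a mismatch of effect measures. Test and sample size are on the π/OR_wmw scale, the named estimate is a difference in medians, and the expected ceiling or floor effects remove the shift assumption that would join the two.

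That they can diverge follows from the definitions and needs no simulation. How often they do rests on the assumed 0-12 distribution and on the interval method. At the design effect the conflict affects about a quarter to nearly two-thirds of significant trials (26% with the order-statistic method, 44-64% with the bootstrap), mostly as a lower limit of exactly 0. With an OR_wmw interval, disagreement falls to about 0.2-0.6% of all trials. This should be fixed, but it does not threaten the validity of the primary test.

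**What to change.** In Primary analysis, replace the sentence on the difference in medians with wording such as: *The primary treatment effect will be reported as π and OR_wmw with a 95% confidence interval consistent with the Wilcoxon-Mann-Whitney test, so that it can be compared with the OR_wmw of 2.0 used for power. Group medians and their difference will be given as descriptive summaries.*

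The cost is one sentence. The test, sample size, power statement and data collection do not change. Making the change before unblinding avoids a choice of effect measure after the results are known.

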#### Secondary analyses

All secondary analyses will be for descriptive purposes only. Point and interval estimates of the effect of the intervention on LEM scores at 6 and 12 months will be determined using a linear mixed model. The baseline LEM score will be included in the model as a covariate. Analyses for frailty, TUG and activity patterns as measured by CHAMPS and accelerometry will follow that of LEM. Types of management received and adherence to prescribed therapies will be described separately for each group. Analyses will be conducted at 6 months for descriptive purposes only.

## Discussion

We have adopted the Integrated Knowledge Translation model for this project. We recognize the need for post-discharge hip fracture management and have worked together with clinicians to develop this model. Our preliminary work included interviews with seniors to pilot our outcome measures and better understand barriers and enablers to taking part in exercise after hip fracture. In addition, our team includes knowledge users such as our partners within the local health authority, and clinicians who work daily with this population. We have previously shown effectiveness of our falls clinic model [67] and now extend this work with a higher risk population. We aim to test a delivery model that would be acceptable to both older adults, their caregivers and clinicians; and will complete an economic evaluation in parallel to determine operating costs and cost-effectiveness and cost-utility of the intervention.
